## Methods and analyses

### The MindMatters intervention

Originally developed in Australia in the late 1990s, MindMatters is a universal mental health promotion intervention for primary and secondary schools that takes a holistic approach to school health promotion. The German adaptation (www.mindmatters-schule.de) took place from 2002 to 2005, with 32 schools implementing the intervention modules over an 18-month period. It is based on the concept of the ‘Good and Healthy School’, which proposes a close link between health and education. This approach starts from the educational quality of the school and tries to promote this quality through health interventions. Health is thus seen as a driving force or an essential determinant of successful educational processes [18]. In line with the Health Promoting School approach, the Good and Healthy School is a holistic or whole-school approach that addresses different target groups (pupils, teachers, parents) and, in addition to individual behaviour, the wider school environment. In addition to the general promotion of mental health and the prevention of mental disorders in pupils, MindMatters aims to:Develop a school culture where all school members feel safe, valued and includedSupport schools in building or developing a caring school culture and networking between schools and the school environmentContribute to improvements in teaching and learning, thereby enhancing the quality of education in schools

For secondary schools, the intervention consists of a total of nine modules. Three of these modules are related to school development and address the development of school structures, policies and community partnerships to promote mental health. In addition, there are five subject-specific teaching modules dealing with topics such as preventing bullying, making friends, dealing with stress, mental disorders and experiences of loss and grief (Additional file 1: Overview of the German-language MindMatters intervention).

Since 2012, a separate intervention module for primary schools called ‘Learning Together with Emotions’ has been launched [19]. It supports primary schools in promoting social-emotional learning (SEL) in the classroom and is based on the five broad and interrelated domains of competence developed by the Collaborative for Academic, Social and Emotional Learning [20]. These include the following:Self-awareness, i.e. the ability to understand one’s own emotions, thoughts and valuesSelf-management, i.e. the ability to manage one’s emotions, thoughts and behaviour effectively in different situationsResponsible decision-making, i.e. the ability to make caring and constructive choices about personal behaviour and social interactions in different situationsRelationship skills, i.e. the ability to establish and maintain healthy and supportive relationships and to navigate an environment with diverse individuals and groupsSocial awareness, i.e. the ability to understand the perspectives of and empathise with others

Each competence area is covered by a teaching unit with five exercises and a final activity (e.g. a game, a song), which can be used by the teacher as a flexible resource at the curricular level (i.e. 30 activities in total). There are different variations for each exercise, which allows the intervention to be adapted to the individual needs of the pupils (different learning levels, e.g. exercises for children with and without literacy skills). Each exercise takes between 15 and 30 min. to complete, depending on the variation chosen. In addition, there are seven exercises that can be used to complement or introduce the units (e.g. setting class rules, finding each other in groups, pupils as researchers). As shown in Additional file 1, the teaching module is complemented by the SchoolMatters school development module. Designed as a basic module, SchoolMatters aims to support schools in creating structures and processes to maintain and promote mental health (e.g. conducting a needs assessment, developing a project plan, establishing a MindMatters school team, building partnerships with community stakeholders).

The intervention materials are primarily considered as a flexible resource to be used by the teacher according to the needs of the school. Although a sequence of exercises is provided within the teaching module, there is a low degree of standardisation in the implementation of the intervention. The main target group for implementation are teachers, school principals and school teams who can voluntarily attend a MindMatters training. A website (www.mindmatters-schule.de) provides training dates and access to a toolbox of further classroom exercises.

### Study design

This study is an ongoing two-arm cluster-randomised controlled superiority trial (CRCT) with baseline and post-measurement. The study protocol follows the standard protocol for clinical trials according to the SPIRIT 2013 statement (Fig. 1; Additional file 2: SPIRIT checklist) [21].

**Fig. 1 Fig1:**
[figure not shown]
SPIRIT figure

Primary schools are eligible to participate if (1) they are from one of the three federal states (North Rine-Westphalia, Rhineland-Palatinate, Schleswig–Holstein), (2) they have not implemented the MindMatters intervention in the past and (3) they agree to be assigned to either the intervention or control group. After enrolment, eligible schools will be randomly assigned 1:1 to either the intervention or control group using the Microsoft Excel random number function, with randomisation stratified by subgroups: federal state, school size, social gradient and level of activity in school health promotion. Within the subgroups, each school will be assigned a random number, with the proviso that, for example, schools with large random numbers will be assigned to the intervention group and schools with small random numbers will be assigned to the control group. Randomisation and communication with schools will be carried out by the investigators. Schools will be informed individually by e-mail of the outcome of the group allocation. Data will be collected at baseline and again 18 months after the start of the intervention, including the perspectives of pupils and teachers (both baseline and post-test) as well as parents (post-test only). While the MindMatters intervention is implemented in the intervention schools according to defined criteria, no intervention is implemented in the control schools. The trial flow of the evaluation study is shown in Fig. 2. The trial has been approved by the Ethical Review Board of Fulda University of Applied Sciences (Nr. 3.1.9.2), the Ministries of Education in Rhineland-Palatinate and Schleswig–Holstein, and registered with the German Clinical Trials Register (DRKS00023762).

**Fig. 2 Fig2:**
[figure not shown]
Trial flow chart

### Sample size calculation

In this study, schools represent the intervention clusters in which classes and pupils are nested. The power analysis relates to the individual pupil level, taking into account the cluster effect by including the intraclass correlation (ICC). There is no ICC estimate for mental disorders in the target age group, but it is estimated to be rather low compared to substance use or risky behaviour and is therefore set at *p* = 0.01 for the power analysis [22]. While the medium effects can be expected at the level of knowledge for primary school pupils (*d* = 0.5), small effects (*d* = 0.1 to 0.3) are assumed at the level of competence due to the short study period. Given the most recent findings on the prevalence, it is expected that the prevalence of mental health problems in the intervention group will be at most four percentage points lower than in the control group at the post-test.

Assuming an alpha level of 5% and a statistical power of 0.80, the estimated sample size is 2066 (with equal allocation to both groups, i.e. 1033 pupils in the intervention group and 1033 in the control group, https://www.sealedenvelope.com/power). Taking into account an intra-class correlation of 0.01 and a number of approximately 15 pupils per class with parental consent and actually present on the day of the survey, the required total sample size increases as follows: (1 + (15 − 1) × 0.01) × 2066 = 2355. Based on previous studies in primary school education, an attrition rate of about 10% is calculated for the pre-post survey at the pupil level across the different measurement points, so that a total sample of 2615 pupils from 174 classes is required for the baseline test. It is planned to implement this with a total of 40 participating primary schools (20 in the intervention group and 20 in the control group).

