## Abstract

**Background:**

The prevalence of mental health problems in childhood and adolescence has increased significantly, not least due to the COVID-19 pandemic in Germany and other countries worldwide. Although holistic school interventions to promote mental health and prevent mental health problems are considered promising, there is currently uncertainty about their effectiveness due to evaluation studies with heterogeneous methodological quality. This paper presents the study protocol for the evaluation of the primary school module of MindMatters.

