## Introduction

Although childhood and adolescence are considered comparatively healthy periods of life, especially in industrialised countries, researchers point to an epidemiological shift that places greater emphasis on non-communicable diseases (NCDs) such as mental health problems [1]. Indeed, an analysis of the Global Burden of Disease (GBD) 2015 study revealed that mental disorders were the second leading cause of disability-adjusted life years (DALY) among children aged 5–14 years in America and Europe [2]. A meta-analysis of 41 studies from 27 countries estimated a global pooled prevalence of mental disorders in children and adolescents of 13.4%, with the highest prevalence rates found for anxiety and disruptive disorders [3]. Summarising studies using the General Health Questionnaire (GHQ-12), a recent review found a global prevalence of common mental disorders of 25 to 31% depending on the cut-off value used [4]. However, the mental health of young people has deteriorated since the COVID-19 pandemic. In their recent rapid review, Schlack et al. [5] found evidence of significant increases in the proportion of children and adolescents with lower quality of life, higher levels of stress or more symptoms of specific mental disorders, particularly in the early phase of the pandemic. Results from the German longitudinal COPSY study indicate an increase in overall mental health problems from 18% (pre-pandemic) to 29% (mid-2020) to 31% (early 2021), which remained at a high level in the last wave (end 2021, [6]).

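### The 2066-pupil calculation prints no control prevalence; it back-solves to about 14%, while the protocol's own latest figures are 29–31%, where four points has roughly 52–54% power

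*Protocol article*

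**What the plan says.** In the protocol article, under Sample size calculation, the planned effect is introduced with "Given the most recent findings on the prevalence, it is expected that the prevalence of mental health problems in the intervention group will be", and the sentence ends "will be at most four percentage points lower than in the control group at the post-test". The next paragraph continues: "Assuming an alpha level of 5% and a statistical power of 0.80, the estimated sample size is 2066", that is 1033 per arm. A design effect of 1.14 (ICC 0.01, 15 pupils per class) and 10% attrition then bring the baseline requirement to 2615. Neither the control-group prevalence nor the sidedness of the test is printed, and the recent findings carry no reference.

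The Introduction describes, for Germany, "an increase in overall mental health problems from 18% (pre-pandemic) to 29% (mid-2020) to 31% (early 2021), which remained at a high level"; the final wave cited dates from the end of 2021. It also gives 13.4% as a global pooled prevalence of mental disorders, and 25 to 31% for common mental disorders. The abstract opens on the same theme: "The prevalence of mental health problems in childhood and adolescence has increased significantly, not least due to the COVID-19 pandemic".

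The Discussion concedes that the ICC was severely underestimated (pilot values 0.03 to 0.07) and that power for small effects may be inadequate. It does not mention the base rate.

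**The concern.** For a fixed absolute difference, the sample size of a two-proportion comparison depends directly on the control rate, because the variance p(1−p) grows as p moves from 14% towards 50%. The section ties its assumption to recent prevalence findings, and the only recent series in the article that uses the same term, mental health problems, stands at about twice the rate that the sample size implies.

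At stake is the only 80% power statement in the article. If the control rate is near the figures the article itself reports, a four-point difference in prevalence has roughly even odds of detection even on the planning ICC. A reader who relies on the printed 80% would then take a null prevalence comparison as stronger evidence against a four-point effect than it is. The ICC admission in the Discussion does not cover this, because correcting the ICC leaves the base rate as it was.

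**Working it through.** **Inputs.** Alpha 5%, power 0.80, difference 0.04, 1:1 allocation, 1033 per arm, ICC 0.01, 15 pupils per class, 10% attrition (Sample size calculation). Prevalences of 13.4%, 18%, 29% and 31% (Introduction). Pilot ICCs 0.03 to 0.07 (Discussion). Assumption: two-sided test, since sidedness is not stated; one-sided results are given alongside.

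**Formula** (normal approximation, unpooled variance):

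n per arm = (z_α + z_β)² × [p_c(1−p_c) + p_i(1−p_i)] / (p_c − p_i)²

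Two-sided, (1.960 + 0.8416)² = 7.849.

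**Reproducing 2066.** For 14% versus 10%, the variance sum is 0.1204 + 0.0900 = 0.2104, and n = 7.849 × 0.2104 / 0.0016 = 1032.1. Rounded up this is 1033 per arm, 2066 in total, an exact match. Solving for p_c at n = 1033 returns 14.0%. Neighbouring rates miss: 13% gives 957 per arm and 15% gives 1106. The later steps follow: 2066 × 1.14 = 2355, and 2355 / 0.9 = 2617 against the printed 2615.

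**Other readings.** The pooled-variance formula gives 1035 per arm at 14%. One-sided at 5%, 18% versus 14% gives 1036 per arm (2072), close but not exact; 17% versus 13% one-sided with continuity correction gives 1034. The Introduction's 13.4% gives 988 per arm two-sided (1976 in total).

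**Moving the control rate, four points kept.** Power = Φ(0.04 / √(variance sum / 1033) − 1.960). At 31% versus 27% the variance sum is 0.2139 + 0.1971 = 0.4110, the standard error is 0.01995, and 0.04 / 0.01995 − 1.960 = 0.045, so power is 52%.

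| Control rate | n per arm for 80% (two-sided) | Two-sided power, 1033 per arm | One-sided power, 1033 per arm |
|---|---|---|---|
| 14% | 1033 | 80% | 88% |
| 18% | 1315 | 70% | 80% |
| 29% | 1930 | 54% | 66% |
| 31% | 2017 | 52% | 64% |

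No variant tried brings 2066 near 29–31%. At 31% the total before clustering would be 4034, and 4034 × 1.14 / 0.9 ≈ 5110 at baseline. Solving the power formula for the difference at 31% with 1033 per arm and 80% power gives about 5.5 points.

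**Adding the pilot ICCs.** Keep 2355 analysed pupils and 15 per class. The design effect is 1 + 14 × ICC, and effective n per arm is 2355 / (2 × design effect).

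| ICC | Design effect | Effective n per arm | Power at 14% | Power at 31% |
|---|---|---|---|---|
| 0.01 | 1.14 | 1033 | 80% | 52% |
| 0.03 | 1.42 | 829 | 71% | 44% |
| 0.07 | 1.98 | 595 | 57% | 33% |

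**The case against.** The case on the other side has real substance.

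- *The 14% is not printed.* It is back-solved, and it depends on a two-sided reading. Read one-sided, 18% versus 14% comes within six pupils of 2066, and 18% is the article's pre-pandemic German figure. This stands, so 14% is the likeliest input and not a documented one. Neither reading reaches 29–31%.
- *The recent findings are not referenced.* The section sets its ICC for mental disorders, for which the Introduction gives 13.4%, and at that rate 1033 per arm would have about 82% power. A reader might infer a proven contradiction with the 31% figure; the text does not prove which source was meant. Still, the sizing sentence speaks of mental health problems, the term used for the 18–29–31% series, and 13.4% does not reproduce 2066.
- *Timing.* The Discussion calls the power calculation a priori and the trial was registered on 5 January 2021, so the early-2021 figure may postdate it. This stands for 31%; the 29% figure is from mid-2020 and gives 54%, almost the same answer.
- *Population and time point.* The 29–31% covers children and adolescents, with a last wave at the end of 2021. The trial studies primary pupils with a revised, picture-supported SDQ, and data collection ran to September 2023. Recruitment in 2021–22 therefore does not establish the post-test control rate, which no document gives.
- *The absolute difference need not stay at four points.* With the same relative reduction as 14% to 10%, power would be 90% at 18% and above 99% at 31% (versus 22.1%). But the article states its effect as an absolute difference, and as a maximum, so a larger one at a higher base rate would contradict its own ceiling.
- *The planned analysis is different.* The main analysis is a baseline-adjusted multilevel regression, and Table 1 lists the SDQ as a sum score. This stands in full.

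**Conclusion.** The sample size section appeals to recent prevalence findings, prints no control rate, and arrives at a total that fits about 14% (two-sided) and does not fit the 29–31% that the article itself reports as most recent. On those rates the 80% claim is not met: two-sided power for four points is about 54% to 52%, or 66% to 64% one-sided, and about 70% two-sided at 18%. With the pilot ICCs it falls to about 44–33% at 31%, and even at 14% it is about 71–57%.

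These figures rest on the four-point absolute difference, the normal-approximation comparison of two proportions, and control rates taken from the Introduction and not measured on the trial's instrument. Because four points is given as the most that is expected, they are upper values for that comparison.

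Two stronger readings are tempting and not supported. One is that the trial's power is 52%: that number belongs to the prevalence comparison used for sizing at one assumed control rate, and the power of the baseline-adjusted SDQ model cannot be derived from it. The other is that 14% versus 10% is the only possible input: it is the only exact whole-percentage match with a four-point difference on the two-sided formula, and a one-sided reading allows 18% versus 14% approximately.

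**What to change.** In the Sample size calculation section:

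1. State the control prevalence used, its source, and whether the test is one- or two-sided.
2. Replace the single 80% claim with power for four points over control rates from 14% to 31%, under ICC 0.01 (two-sided: 80% at 14%, 70% at 18%, 54% at 29%, 52% at 31%) and under the pilot ICCs of 0.03 to 0.07 (about 71–57% at 14% and 44–33% at 31%, with 2355 analysed pupils and 15 per class). Add the detectable difference of about 5.5 points at 31% under ICC 0.01. Giving the ICC 0.01 figures alone would repeat an assumption that the Discussion already rejects.
3. Say that these figures apply to the two-proportion comparison and not to the baseline-adjusted model of SDQ scores.
4. If 14% is kept, name its basis and drop the appeal to the most recent findings.

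The cost is one recalculation and revised wording. Enrolment does not change. The stated power becomes less favourable.

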### Recruitment and strategies for achieving adequate participant enrolment

As MindMatters is a complex intervention that addresses several levels, a period of 4 months is estimated for the schools to be recruited. Recruitment takes place in a total of three federal states (Rhineland-Palatinate, North Rhine-Westphalia and Schleswig–Holstein), with all primary schools being invited to participate. As a first step, all school principals will be invited to participate in the study by email. After a reminder by post, all schools will be contacted by telephone by the study team. Schools with a positive response will be contacted personally and will be informed about the process of the study. After agreeing to participate, the principal receives a short online questionnaire to assess the school’s general conditions (e.g. current implementation of school health promotion).

At the pupil level, data response is ensured by having trained academic staff collecting the data in the classroom. The success rate depends largely on the number of pupils with parental consent. To increase the response rate of parental consent forms, parents receive a detailed information letter. To increase the response rate among parents and teachers, the survey is offered both online and in paper–pencil form. The return of data is continuously monitored and reported back to schools at regular intervals. The feedback explicitly states that the significance of participating in the study is highly dependent on the level of data response. To encourage retention and completion of follow-up, schools are promised individual feedback on results at the end of the study. In addition, intervention and control schools will receive regular updates on the status of the study and motivational messages (e.g. greeting cards).

### Measures

The intervention model includes a set of outcomes that unfold gradually in the short-, medium- and long-term levels and can be observed at the school and individual levels (mainly pupils and teachers, Additional file 3: MindMatters intervention model for primary schools) [23]. The primary outcome of this study includes several indicators of pupils’ mental health (e.g. emotional symptoms, conduct problems, prosocial behaviour). According to Nutbeam’s outcome model, these effects are preceded by direct effects at the individual level, such as knowledge or skills, but also at the classroom and organisational levels, such as classroom climate, classroom disruption, integration of health promotion into the school mission or organisational commitment. In line with the basic assumption of the Good Healthy School approach, it is also assumed that improvements in direct outcomes and mental health will have a positive long-term effect on pupils’ educational outcomes (e.g. academic performance, learning behaviour). Finally, the intervention model includes a number of factors that have been shown in previous studies to be relevant to intervention effectiveness. In addition to ‘traditional’ measures of implementation fidelity, such as adherence, dosage or acceptability [24], we included further measures such as health-promoting leadership or readiness for change [25]. Table 1 provides an overview of the measurements.

**Table 1 Tab1:** Overview of study measurements

Construct	Measure	Metric	Method of aggregation	Source
Mental and behavioural problems	SDQ [26]	Ordinal	Sum score	PU, T, PA
Emotion related knowledge	Self-developed	Nominal	Sum score	PU
Social-emotional skills	FEESS 1–2 [27]	Nominal	Sum score	PU
Diagnostic skills	COAKTIV [28]	4-point scale	Mean	T
Classroom disruption	FASS [29]	5-point scale	Sum score	T
Mobbing	PISA [30]	4-point scale	Sum score	T
Classroom climate	QuaSSU [31]	4-point scale	Sum score	T
Health Promoting School mission	Extended SEP scale on health promotion [32, 33]	5-point scale	Mean	T
Organisational commitment	COMMIT [34]	4-point scale	Mean	T
Academic performance	Adapted by [35]	5-point scale	Mean	T, PA
Learning behaviour	Adapted by [35]	5-point scale	Mean	T, PA
Implementation of MindMatters teaching module	Adapted by [36]	Mixed	Weighted sum-score	T
Implementation of MindMatters school development module	Self-developed	Mixed	Weighted sum score	T
Implementation of Health Promoting School	USG [37]	4-point scale	Mean	T (principals)
Whole-school mental health promotion	SSPESH [38]	4-point scale	Mean	T (principals)
Readiness for change	KESS 7, [39]	4-point scale	Mean	T
Health-promoting leadership	HoL [40]	5-point scale	Mean	T
Sex	Self-developed	Nominal		PU, T
Age	Self-developed	In years	Mean	T
Socioeconomic status (classroom level)	NEPS [41]	Percentage	Mean	T
Migration background (classroom level)	NEPS [41]	Percentage	Mean	T

*PU* pupils, *PA* parents, *T* teachers

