### Aims and hypothesis

The study aims to replicate the intervention effects of MindMatters previously identified for primary schools [16, 17] and to examine the additional effects. Based on a confirmatory multicentre trial, a more rigorous study design will be applied, including a comparable control group. At the pupil level, the focus will be on social-emotional skills, mental health and behavioural problems. In addition to replicating the results at the pupil level, the evaluation aims to examine the changes at the organisational and classroom level, e.g. in terms of improved learning and social climate as perceived by teachers. The study will also examine whether pupils’ academic performance can be improved by strengthening their mental health.

The following hypotheses will be tested:Pupils in intervention schools show higher levels of emotion-related knowledge than pupils in control schools.Pupils in intervention schools have higher levels of social-emotional skills and lower levels of mental health and behavioural problems at post-test compared to pupils in control schools.Teachers in intervention schools report improved diagnostic skills, improved learning and social climate and reduced classroom disruption at post-test compared to teachers in control classes.Parents and teachers of pupils in intervention schools report improved academic performance and learning behaviour compared to parents and class teachers in control schools.Intervention schools with higher implementation quality show greater effectiveness in terms of pupils’ social-emotional skills and mental health, and classroom outcomes such as bullying, classroom climate and disruption, compared to schools with lower implementation quality.

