#### Mental health outcomes

The change in mental and behavioural problems from baseline to post-assessment is measured using the German version of the Strengths and Difficulties Questionnaire (SDQ). It contains five subscales (hyperactivity, emotional symptoms, conduct problems, peer problems and prosocial scale) with five items for each dimension. In order to increase the comprehensibility and applicability for primary school children, the SDQ items have been revised, and each item has been visualised with a picture. The pupil survey is administered using an innovative tablet computer-based procedure and was pre-tested in June 2021 with 908 pupils in 10 primary schools and 43 classes in North Rhine-Westphalia.

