Statistical analyses will be performed using the latest version of STATA (Stata Corp., College Station, TX, USA). The main analysis will consist of a multilevel regression in which the primary outcomes are predicted at the pupil level using group status (intervention versus control group), controlled for baseline condition. Group status will be included in the model as a fixed effect and a random intercept will be provided for the cluster variables (study region, school, class). Furthermore, all variables with differences between the intervention and control group at baseline will be included in the model. Further mediation analyses will investigate which mediating mechanisms can be identified. It is assumed that the change in mental health outcomes is caused by improvements in proximal (i.e. direct and class/organisational) outcomes. This requires that the group status (i.e. the intervention) is correlated with the proximal outcomes and that the proximal outcomes are significantly related to the distal outcomes. Mediation effects will be examined using the Baron and Kenny partial correlation analysis approach and structural equation models [44, 45]. Moderator analyses will also examine which school-level factors (e.g. size, social gradient) are associated with or influence the impact of MindMatters. Moderator effects are tested using interaction terms in the regression model. The analysis will first be conducted according to the intention-to-treat principle and additionally compared with a per-protocol analysis. Analysis sample 1 includes all those for whom data are available at both measurement points (complete case analysis, as randomised). Analysis sample 2 includes all those reached at baseline (ITT as randomised). Analysis sample 3 includes all those with data available at both measurement points, and schools without intervention are included in the control group. Multiple imputation is used for missing values. To ensure the methodological quality of all analyses, statistical advice is provided by an independent institute.

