## Discussion

This study protocol documents the two-arm cluster randomised controlled trial with baseline and post-assessment for MindMatters primary schools, a holistic school-based intervention to promote mental health in school children. While the overall intervention targets children and adolescents in primary and secondary schools, this study focuses on the primary school module, for which there is no previous evidence. Reductions in mental and behavioural problems in children will be the primary outcomes, preceded by improvements in knowledge and social-emotional skills, as well as organisational improvements such as classroom climate, classroom disruption and organisational commitment. In addition, we expect these intervention effects to have a positive long-term impact on pupils’ educational outcomes.

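### A trial called confirmatory leaves its primary outcome as an open list of SDQ indicators, with no single primary score or informant and no rule for success

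*Protocol article*

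**What the plan says.** - **Status of the trial** (Aims and hypothesis): "Based on a confirmatory multicentre trial, a more rigorous study design will be applied, including a comparable control group".
- **Primary outcome** (Measures): "The primary outcome of this study includes several indicators of pupils’ mental health (e.g. emotional symptoms, conduct problems, prosocial behaviour".
- **Primary outcome again** (Discussion): "Reductions in mental and behavioural problems in children will be the primary outcomes". The abstract describes it in the same way.
- **Instrument** (Mental health outcomes): "It contains five subscales (hyperactivity, emotional symptoms, conduct problems, peer problems and prosocial scale) with five items for each dimension". The same paragraph frames the outcome as a change: "The change in mental and behavioural problems from baseline to post-assessment is measured using the German version of the Strengths and Difficulties Questionnaire (SDQ".
- **Informants** (Table 1): "Mental and behavioural problems SDQ [26] Ordinal Sum score PU, T, PA", that is, pupils, teachers and parents. Study design gives the timing as "including the perspectives of pupils and teachers (both baseline and post-test) as well as parents (post-test only".
- **Main analysis** (Data collection, management and statistical analysis): a multilevel regression in which "the primary outcomes are predicted at the pupil level using group status (intervention versus control group), controlled for baseline condition". No order of testing, composite rule or adjustment is given.
- **Sample size** (Sample size calculation): alpha 5%, power 0.80 and a prevalence of mental health problems at most four percentage points lower with the intervention. This gives 2066 pupils, then 2355 after the design effect and 2615 after attrition.

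**The concern.** A confirmatory trial needs to fix in advance the one result, or the defined set of results, on which it will be judged. Here the list is open and the outcomes are plural. Several SDQ scores from more than one informant could each be presented as the primary result, and a reader of the final report could not tell whether the one emphasised was chosen beforehand.

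The content of the list is also unclear. Measures counts prosocial behaviour among the primary indicators. The abstract and Discussion speak only of reductions in problems, and the limitations paragraph names prosocial items as one reason why the SDQ may be a poor proxy for mental disorders.

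The sample size does not settle the matter. It powers one binary comparison, and no SDQ cut-off, subscale or informant is linked to it.

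At stake are the meaning of a positive result and, if several indicators are tested without control, the type I error of the main claim.

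**Working it through.** **1. The plan's own figure.** The control prevalence is not stated, so it has to be back-solved. With 14% versus 10% (an assumption), two-sided alpha 5% and power 0.80:

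n per arm = (1.960 + 0.842)² × (0.14×0.86 + 0.10×0.90) / 0.04² = 7.849 × 0.2104 / 0.0016 ≈ 1032.1, rounded up to 1033, total 2066.

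This matches. The next steps are (1 + 14×0.01) × 2066 = 1.14 × 2066 = 2355, and 2355 / 0.9 ≈ 2617 against the stated 2615, a trivial difference. The calculation therefore supports one binary endpoint at one 5% test.

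**2. How many primary tests the text allows.** The SDQ has five subscales.
- Pupils only: 5.
- Pupils and teachers, both measured at baseline and post-test: 10.
- Parents are surveyed at post-test only. Their ratings cannot give a change from baseline or enter a model controlled for baseline condition, so they are left out of the main count.

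**3. Chance of at least one false rejection with no true effect**, if each test were done at two-sided 5% without adjustment. For k independent tests it is 1 − 0.95^k. For a false claim of benefit only, it is 1 − 0.975^k. For correlated tests the values come from simulated normal test statistics with equal correlation r between subscales and, for ten tests, the same value between informants. The article gives no correlations, so r is assumed.

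| Tests | Any rejection, r = 0 | Any rejection, r = 0.5 | Benefit only, r = 0 | Benefit only, r = 0.5 |
|---|---|---|---|---|
| 5 (pupils) | 1 − 0.95^5 = 22.6% | 18.3% | 1 − 0.975^5 = 11.9% | 9.2% |
| 10 (pupils + teachers) | 1 − 0.95^10 = 40.1% | 31.1% | 1 − 0.975^10 = 22.4% | 15.6% |

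The reference values for a single test are 5% and 2.5%.

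**4. Why not keep all indicators and split alpha?** On the back-solved model with 1033 per arm before clustering, a Bonferroni level of 0.05/5 = 0.01 lowers power for each test from 80% to about 59%. At 0.05/10 = 0.005 it is about 50%. Restoring 80% for five tests would take 3072 pupils before clustering, against 2066. Naming one primary outcome avoids that loss.

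**The case against.** **The article does not say that each indicator is tested at 5%.** This is correct. The level appears only in the sample size paragraph, and an analysis plan that is not shown may adjust for multiplicity. The absence of an adjustment is therefore not the point here, and the error rates above are conditional. The undefined primary outcome remains, because the article addresses it and leaves it open.

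**Pupil self-report is the natural reading.** The abstract places the primary outcomes at pupil level, the hypotheses assign teacher reports mainly to classroom and academic outcomes, and the Discussion stresses children's own views. This carries weight and favours the five-test figures. It does not close the question: pupil level describes the unit of analysis, and Table 1 lists three sources for the SDQ.

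**Table 1 gives a sum score.** That could mean one total, but it could equally mean a sum within each subscale. The mention of several indicators, and the pilot ICCs reported for separate subscales, point to the latter.

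**Mental and behavioural problems may be shorthand for the whole SDQ.** This is plausible, so the mismatch over prosocial behaviour is an ambiguity rather than a firm contradiction.

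**Stronger readings that the documents do not support.** A reader might count five subscales for three informants, 15 tests, and quote 1 − 0.95^15 = 53.7%. That counts parent ratings, which do not fit the stated model. A reader might also take the two-sided rates as the chance of a false claim of benefit, which is only about half as large. Finally, a reader might infer that teachers, who deliver the exercises, could supply the primary effect. Nothing names teacher ratings as primary, and rater awareness is a separate question of bias.

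**Conclusion.** The point holds in this form: the article calls the trial confirmatory but does not fix its primary outcome, informant or success rule, and the powered endpoint matches none of the indicators listed. This is more than missing detail, because the article defines the primary outcome and does so by example and in the plural.

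The consequence for error control is conditional. Under unadjusted two-sided 5% tests, the family-wise error would be about 18–23% for the five pupil-reported subscales and about 31–40% if teacher ratings count too. For false claims of benefit the ranges are about 9–12% and 16–22%. They rest on assumed correlations from 0 to 0.5 and on every subscale being a primary test. The documents do not establish that the trial will be analysed in this way. They do not exclude it either.

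**What to change.** 1. In Measures, name one primary outcome with its score, informant and time point. One suitable choice is the pupil-reported SDQ total problem score at 18 months (hyperactivity, emotional symptoms, conduct problems and peer problems, without the prosocial scale), tested at two-sided 5%.
2. Make the five subscales and the teacher and parent ratings secondary, with Holm adjustment. State that parent ratings are compared without a baseline value.
3. Use the same definition in the abstract, the analysis section and the Discussion.
4. Reconcile it with the sample size: either say how the chosen score relates to the prevalence endpoint, including the cut-off and the control rate, or restate the power for that score.
5. Record this as a dated, disclosed amendment before any analysis by arm. Data collection ran to September 2023 and the protocol version is dated 6 October 2023, so the choice comes after the data were collected. The amendment should say so and confirm that no comparison by arm had been seen.

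The cost is the amendment, a revised power statement and consistent wording, with no new data. The downside is that an isolated subscale or teacher-rated finding can no longer be claimed as the primary result.
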